**Methods and design:**

We planned to employ a randomized, double-blind experimental design, including 40 children receiving sham stimulation and 40 children receiving real stimulation. We will assess clinical scales and perform functional imaging examinations before and after the stimulation. Additionally, we will include age- and gender-matched healthy children as controls and conduct functional imaging examinations. We plan first to observe the therapeutic effects of taVNS. Furthermore, we will observe the impact of taVNS stimulation on the brain network.

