Based on the aforementioned evidence, we designed our protocol with two primary objectives: First, it aims to examine the therapeutic effects of taVNS in individuals diagnosed with HFA; Second, it intends to investigate the process of brain network remodeling after taVNS using functional imaging techniques. We will use graph-theoretic analysis to compare the brain network characteristics of individuals with HFA before and after receiving taVNS. Additionally, we will examine the differences in these characteristics between patients with HFA and healthy controls, considering both structural and functional connectivity perspectives. Our hypothesis posits that taVNS has the potential to enhance the efficiency and flexibility of brain networks in HFA patients, leading to an improvement in their social cognitive abilities.

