## Methods/design

### Study design

The study will be a randomized, double-blind, sham-controlled clinical trial, which will include patients assigned to active taVNS and sham taVNS groups and healthy subjects assigned to a healthy control group (HC). The study timeline of events is listed in **Figure 1**. For included patients, this study consisted of three basic phases: (a) a one-week baseline; (b) a consecutive 12-week treatment period without weekend interruption (Week 1 - Week 12, W1-W12); and (c) a follow-up period of 12 weeks (Week 13 – Week 24, W13 - W24). After enrollment, an interview will be used to acquire general patient information, including age, gender, duration of HFA, family history, and results of the clinical assessment tools during the baseline. Following the baseline period, patients will be assigned to one of the two treatment groups randomly to receive active taVNS or sham taVNS treatment using a random number table, which will be generated by SPSS 25.0 before enrollment of the first patient. During the follow-up period, patients will be evaluated with clinical assessment tools as well as structural and functional imaging scans.

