**Figure 1 f1:**
[figure not shown]
A schematic representation of the study timeline of events.

The treatment condition assignment will remain undisclosed to patients and independent observers who perform clinical assessments and MRI scan technicians until the last interview. Only the technicians performing the taVNS procedure and the physician assigning the randomization without patient contact will be aware of the group information. No communication will be allowed between patients during any phase of the study to maintain blindness.

Patients will be evaluated using the clinical assessment tools at five time points (baseline; W4, the first month of treatment; W12, right after treatment; W16, short-term follow-up; W24, long-term follow-up) (**Table 1**). MRI scan will be acquired at three time points (baseline, W12, and W24). More details regarding the clinical procedures can be found in **Figure 2**; **Table 1**. Healthy subjects in the HC group will be evaluated with the same clinical tools and undergo an MRI scan only once. The clinical endpoints are assessed by blinded observers who are not involved. Furthermore, all dropouts will be documented and reported, specifying the reasons for their withdrawal.

**Table 1 T1:** Measurements at each time point.

Measurements/time point	Recruitment	Baseline	4 weeks	12 weeks	16 weeks	24 weeks
Inclusion/exclusion criteria	√	N/A	N/A	N/A	N/A	N/A
Behavioral Checklist for Children with High-Functioning Autism/Asperger’s Disorder	N/A	√	√	√	√	√
ABC	N/A	√	√	√	√	√
CABS	N/A	√	√	√	√	√
SRS	N/A	√	√	√	√	√
WISC	N/A	√	√	√	√	√
MRI scanning	N/A	√	N/A	√	√	√

√, need to be finished; ABC, Autism Behavior Checklist; CABS, Clancy Autism Behavioral Scale; SRS, Social Responsiveness Scale; WISC, Wechsler Intelligence Scale. N/A, Not applicable.

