### Statistical analysis

Basic analyses will be conducted using SPSS 25.0 software. At baseline, independent samples t-tests will be used to determine if there is no statistical difference between the two intervention groups; paired samples t-tests will then be used to examine the differences between mean scores before and after the taVNS intervention to determine the effectiveness of the treatment. Additionally, for the imaging study, we will use two-sample t-tests to compare brain network parameters between the HC and sham groups, as well as paired-sample t-tests to determine brain network parameters between the sham and active groups. Based on age and gender as covariates, a two-sample t-test will be used to compare the small-world properties and global parameters of the anatomical network between the HC group and the sham group. The level of significance for all statistical tests is set at p< 0.05. A Bonferroni correction will be performed on the t-tests utilized to examine group differences in behavioral and brain measurements, to account for multiple comparisons.

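### The sham versus active comparison of brain-network parameters is assigned a paired t-test, although the arms are independently randomised children with no pairs, and no between-arm test of network change is stated

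*Protocol article*

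**What the plan says.** The Statistical analysis section assigns its imaging tests in one sentence: "two-sample t-tests to compare brain network parameters between the HC and sham groups", and "paired-sample t-tests to determine brain network parameters between the sham and active groups". The sentence before it covers the clinical scales: "paired samples t-tests will then be used to examine the differences between mean scores before and after the taVNS intervention". A later sentence adds age and gender as covariates, but only for healthy controls versus sham.

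On how the arms arise, Study design says that "patients will be assigned to one of the two treatment groups randomly to receive active taVNS or sham taVNS treatment". The Abstract gives the numbers as "including 40 children receiving sham stimulation and 40 children receiving real stimulation". The only matching described anywhere concerns the healthy children: "we will include age- and gender-matched healthy children as controls and conduct functional imaging examinations".

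On the objective, the last paragraph of the Introduction lists network remodelling after taVNS as the second of two primary objectives and promises to "compare the brain network characteristics of individuals with HFA before and after receiving taVNS". For the scans, the text under Figure 1 says "MRI scan will be acquired at three time points (baseline, W12, and W24". Table 1 and the Discussion also place imaging at W16.

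**The concern.** A paired t-test analyses differences within pairs. The pair must come from the design: the same child twice, or two children matched in advance. Sham and active children are neither. To run the stated test, someone must line up the two columns in some order, and that order carries no information.

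Three things are at stake.

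- **Reproducibility.** The p-value depends on how the file is sorted.
- **Completeness.** When the arms differ in evaluable size, the surplus children have no partner and are dropped.
- **Relevance.** As worded, the test compares parameter values across arms without reference to baseline. It does not address change in the network, which is the objective.

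The same sentence uses a two-sample test for healthy controls versus sham. The article therefore makes the paired/two-sample distinction and gets it wrong for the only randomised imaging contrast.

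**Working it through.** **1. Is there any pairing?** Study design forms the arms by random assignment from a random number table. No section describes matched pairs of patients or a crossover. Matching is mentioned only for healthy controls. Pairs across sham and active do not exist.

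**2. How many evaluable children per arm?** Sample size estimation uses a mean paired difference of 5, SD 8, alpha 0.05 (two-sided assumed), power 0.90, 20% dropout and 15% invalid MRI. Its figures reproduce:

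- n = (8 × (1.960 + 1.282) / 5)² = 26.9, so 27
- 27 / 0.80 = 33.75, so 34
- 34 / 0.85 = 40

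The evaluable number lies between 27 (both losses) and 40 (none).

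**3. Will the arms be equal?** Assume losses are independent and equally likely in both arms. Each child is then evaluable with probability 0.80 × 0.85 = 0.68. The difference in evaluable numbers has variance 2 × 40 × 0.68 × 0.32 = 17.4, so SD 4.17. The chance of exact equality is about 1 / (4.17 × √(2π)) = 0.10. The mean absolute difference is about 4.17 × 0.798 = 3.3 children. In roughly nine trials out of ten, the test as written would discard valid scans.

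**4. What does arbitrary pairing do to the statistic?** With n per arm:

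- independent: t = (mean difference) / √[(s₁² + s₂²) / n], with 2n − 2 degrees of freedom
- paired: t = (mean difference) / √[(s₁² + s₂² − 2s₁₂) / n], with n − 1 degrees of freedom

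The numerators are identical. The covariance s₁₂ is produced by the row order alone and averages zero. At n = 27 the degrees of freedom are 26 instead of 52 (critical values 2.056 and 2.007). At n = 40 they are 39 instead of 78 (2.023 and 1.991).

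**5. Size of the effect.** Simulation of 100,000 normal data sets per row, two-sided 0.05, pairing chosen without sight of the data. The documents give no effect size for any network parameter. The value 0.625 SD is 5/8 from the CABS planning figures; 0.3 and 0.8 are assumed to show a range.

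| n per arm | Effect (SD) | Paired rejects | Independent rejects | Two pairings disagree |
|---|---|---|---|---|
| 27 | 0 | 5.0% | 5.1% | 2.5% |
| 27 | 0.3 | 18.6% | 19.2% | 5.8% |
| 27 | 0.625 | 60.1% | 61.8% | 8.4% |
| 27 | 0.8 | 81.0% | 82.5% | 5.9% |
| 40 | 0 | 5.0% | 4.9% | 2.0% |
| 40 | 0.3 | 25.9% | 26.6% | 5.7% |
| 40 | 0.625 | 77.7% | 78.7% | 5.4% |
| 40 | 0.8 | 93.6% | 94.2% | 2.2% |

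Other runs with different seeds put the disagreement at 0.625 SD at about 7-9% (n = 27) and 5% (n = 40).

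**6. Is network change tested between arms elsewhere?** The section states three kinds of comparison: before/after on mean scores, healthy controls versus sham, and the paired test for sham versus active. The first has no arm contrast. The second does not involve the active arm. The third does not refer to baseline. None compares change in a network parameter between active and sham.

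**The case against.** The strongest defence is that this is a slip. The Introduction plans a before/after network comparison, and the preceding sentence of the Statistical analysis section uses paired t-tests for before/after scores. The imaging sentence may have meant before/after tests within each arm. On that reading genuine pairs exist, the baseline scan is used, and the row-order and discarded-children problems disappear. This is plausible, but the text says something else and needs correcting either way. Two separate within-arm tests would also not compare change between arms, so the sham control would play no part in testing the network hypothesis.

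A second defence is that the article condenses a fuller plan. That would excuse silence about a longitudinal model, so the missing test of change should not be counted as a separate omission. It does not excuse a test that the article names and that does not fit the design. The missing between-arm test of change counts here because the one sham versus active imaging analysis that is stated does not supply it.

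A third point concerns size, and it stands. A reader might infer that significance would be largely a matter of sorting. Under the 0.625 SD assumption, trying 200 reshuffles of each data set and counting any crossing of 0.05 marks about 38% of data sets as unstable at n = 27 and 26% at n = 40. That is a worst-case count which grows with the number of reshuffles, whereas a trial analyses one order. A reader might also infer inflated false positives; the simulation shows none when the order is chosen blind to outcome.

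**Conclusion.** The point holds. The stated test has no defined pairs in this parallel-group design, and it does not use the baseline scan. Whichever way the sentence is read, a stated primary objective is left without a between-arm comparison of network change.

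The numerical damage from arbitrary pairing is modest: type I error about 5%, power lower by 1 to 2 points, and disagreement between two arbitrary pairings in at most about 9% of data sets under the values tried. These figures assume normal data, equal arms, a two-sided 0.05 level before any Bonferroni correction, and an effect size borrowed from a clinical scale. The case rests on the mismatch between test, design and objective, and does not depend on those figures. The documents do not support the stronger claims that the result would be mostly arbitrary or that the error rate would be inflated.

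**What to change.** Replace the sham versus active imaging sentence with a between-arm comparison of each network parameter at each post-baseline MRI visit. Use a linear model (ANCOVA, or a mixed model across visits) with arm as the factor, adjusted for the baseline value of that parameter. Age and sex are optional covariates. The reported estimate is the baseline-adjusted difference between active and sham. An independent-samples t-test on change from baseline is the minimum that would cure the fault.

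Paired t-tests may stay as within-arm description, labelled as such.

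The visits are W12 and W24. Whether W16 belongs depends on reconciling the text under Figure 1, which gives three imaging time points, with Table 1 and the Discussion, which add W16. That should be settled in the same edit.

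The cost is a change of wording before the data are analysed. The baseline and follow-up scans are already planned, so no further data or participants are needed for this correction.

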### Participants

#### Recruitment of participants

The Beijing Children’s Hospital Department of Psychiatry will recruit participants with HFA diagnoses from clinical practice, and a clinical multidisciplinary team involving two experienced psychiatrists will diagnose patients according to the DSM-5 diagnostic criteria. The inclusion criteria are as follows:

the age range is between 6-12 years old.Wechsler intelligence test IQ of at least 80 for Chinese children.ability and willingness to cooperate with relevant assessments and tests.right-handedness.

The exclusion criteria include:

seizure disorder or other neurological diseases (including brain tumors and craniocerebral trauma).concomitant with other mental disorders, except for attention deficit hyperactivity disorder (ADHD) and obsessive-compulsive disorder (OCD).claustrophobia.impulsivity or aggression.presence of metal products in the body.

Discontinuation and withdrawal criteria:

sudden acute illness who are unable to progress to the next phase in the study.poor adherence, and biased results will be regarded as withdrawing from the study.other uncontrollable factors or self-withdrawal from the study.

In this study, recruitment is set to occur over a period of one and a half years (from August 2023 to December 2024). Beijing primary schools will be recruited to provide healthy controls meeting the following inclusion criteria:

The age range is between 6-12 years old.IQ of at least 80.right-handedness.

Exclusion criteria include:

diagnosis of neurological or mental disorders.claustrophobia.presence of metal products in the body.

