#### Sample size estimation

Power Analysis and Sample Size Software version 15.0 (PASS, NCSS Statistical Software, Kaysville, UT, USA) was used to determine the study’s sample size. An alpha of 0.05 and a power of 0.9 are used in the study. Based on preliminary trial results, the Clancy Autism Behavioral Scale (CABS) score indicates a curative effect, so the mean and standard deviation of the paired differences are 5 and 8, respectively (15). The PASS software calculation resulted in a minimum requirement of 34 participants per group, accounting for an estimated 20% dropout rate. Considering a 15% rate of invalid MRI data based on previous experience, a minimum of 40 subjects will be recruited per group. Therefore, 40 patients will be enrolled in each group, totaling 80 patients for the study.

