#### Network analysis

The small-world properties, global properties, and local properties of brain networks will be analyzed using graph theory. There are five small-world properties: clustering coefficient (Cp), characteristic path length (Lp), normalized clustering coefficient (Gamma, γ), normalized characteristic path length (Lambda, λ), and small-worldness (Sigma, σ) (50, 51). A network is regarded to have small-world features when γ >> 1, λ ≈1, and σ > 1 (48, 52). Global network properties consist of global efficiency (Eg) and local efficiency (Eloc). Nodal properties, or local properties, include nodal efficiency (NE), betweenness centrality (BC), and nodal degree centrality (DC) (51, 53). A node’s NE can be measured as its capacity to transmit information to other nodes, its BC as its capacity to influence the flow of information between all other nodes, and its DC can be measured as the number of edges it connects with (52, 54).. In a previous publication, these network measures were defined in detail (54).

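### Age and gender adjustment is stated only for anatomical small-world and global parameters, leaving the functional and nodal comparisons with healthy controls unadjusted as written

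*Protocol article*

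**What the plan says.** Two sentences in the protocol article, Statistical analysis, govern the comparison with healthy controls.

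- General sentence: "we will use two-sample t-tests to compare brain network parameters between the HC and sham groups". No covariates are named.
- Specific sentence, later in the same paragraph: "Based on age and gender as covariates, a two-sample t-test will be used to compare the small-world properties and global parameters of the anatomical network", again for HC against sham.

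The measures to which these apply are set out elsewhere.

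- The Introduction plans the comparison of patients with healthy controls "considering both structural and functional connectivity perspectives".
- Network analysis lists five small-world properties and two global ones (global and local efficiency). It then adds a nodal set: "Nodal properties, or local properties, include nodal efficiency (NE), betweenness centrality (BC), and nodal degree centrality (DC").

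On the control group itself, the Abstract says "we will include age- and gender-matched healthy children as controls and conduct functional imaging examinations". Recruitment of participants says "Beijing primary schools will be recruited to provide healthy controls meeting the following inclusion criteria", and the criteria are "The age range is between 6-12 years old.IQ of at least 80.right-handedness", followed by exclusions.

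Two further provisions bear on who is analysed. MR preprocessing drops subjects whose head moves more than 2 mm or 2 degrees. Sample size estimation expects 15% of MRI data to be invalid.

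**The concern.** Healthy children come from schools and patients from a psychiatric clinic. Randomisation does not balance these groups, and the age band covers six years of childhood. If a network metric varies with age or sex, any difference in age or sex between the analysed groups enters an unadjusted contrast as bias.

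By adjusting the anatomical small-world and global parameters, the plan itself treats age and gender as relevant to network metrics in these children. It gives no reason why they would matter for anatomical global efficiency but not for functional global efficiency or nodal degree.

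Two consequences follow. The functional and nodal contrasts with HC are open to confounding that the plan handles elsewhere. Also, a structural finding adjusted for age and gender cannot be set directly beside an unadjusted functional one, because an apparent disagreement could come from the covariates alone. The Introduction wants both perspectives, so that comparison will be made.

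There is also a problem of method. A two-sample t-test takes no covariates, so the adjusted analysis as named cannot be run. It needs a linear model.

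**Working it through.** **1. Coverage of the adjustment, by type of HC contrast**

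| Network | Small-world | Global | Nodal |
|---|---|---|---|
| Anatomical (structural) | age and gender named | age and gender named | none named |
| Functional | none named | none named | none named |

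Four of the six cells fall only under the general sentence, which names no covariates.

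**2. The plan's own figures**

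The plan states no size for the HC group and no power for the HC contrast. Its only figures are for the patient groups, with "An alpha of 0.05 and a power of 0.9 are used in the study" and a paired CABS difference of mean 5 and SD 8. These reproduce with a two-sided normal approximation:

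- n = (8 × (1.960 + 1.282) / 5)² = 26.9, so 27
- 27 / 0.80 = 33.75, so 34 after 20% dropout
- 34 / 0.85 = 40 after 15% invalid MRI

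They are not in dispute here.

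**3. Illustration of possible bias**

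Inputs:

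- Analysed sham patients: 40 × 0.85 = 34 (from Sample size estimation).
- Analysed controls: 40 (assumed; the plan gives no number).
- Age SD: 6 / √12 = 1.73 years (assumes ages uniform over 6 to 12).
- Correlation of age with the metric: 0.3 (assumed).
- Age gap between the analysed groups: 0.1 to 1 year (assumed).
- No true group difference; two-sided test at 0.05 with no multiplicity correction; 34 + 40 − 2 = 72 degrees of freedom.

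Formulas:

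- Bias in SD units = 0.3 × gap / 1.73.
- Standard error in SD units = √(1/34 + 1/40) = 0.233.
- Noncentrality = bias / 0.233. The rejection rate comes from the noncentral t distribution.

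| Mean age gap | Bias (SD) | Noncentrality | False rejection at 0.05 |
|---|---|---|---|
| 0 | 0 | 0 | 5.0% |
| 0.1 year | 0.02 | 0.07 | 5.1% |
| 0.25 year | 0.04 | 0.19 | 5.4% |
| 0.5 year | 0.09 | 0.37 | 6.6% |
| 1 year | 0.17 | 0.74 | 11.4% |

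**4. With a Bonferroni correction**

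The plan applies Bonferroni to group differences in brain measurements but does not give the number of tests. For an assumed family of seven (five small-world plus two global), the per-test level is 0.05 / 7 = 0.7%. The 1-year gap then gives 2.5% against that nominal 0.7%. The correction lowers the rate but leaves the bias of 0.17 SD in the estimate.

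**The case against.** **Matching is the stated safeguard.** The Abstract applies it to the control group as a whole, so it covers functional and nodal contrasts too. This stands, and it limits the concern. Gaps of the size that good matching would leave (0.1 to 0.25 year) barely move the error rate. However, matching acts at enrolment, while the contrast is made on usable scans. Exclusions for motion and invalid MRI can reopen an imbalance, and only adjustment deals with that at analysis.

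**A reader might infer that the Abstract and the recruitment section define the comparator in two ways.** The documents do not support this. Eligibility criteria say who may enter, whereas matching says how controls are chosen among those eligible. The recruitment section is silent on matching and does not contradict it. A condensed article may leave the matching procedure to the full protocol, so its absence is not a finding.

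**The absence of covariates is read from silence.** The plan never says that functional and nodal contrasts exclude covariates, and a fuller analysis plan may list them. The specific sentence can also be read as refining the general one, so it is not established that the anatomical global parameters have two competing analyses. Both points are fair. What remains is that the text names covariates for an explicitly bounded subset, and an analyst following it would leave the rest unadjusted.

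**A reader might also take 11.4% as the plan's error rate.** It is not. It presupposes a 1-year gap, which means that matching has failed, and it ignores the planned Bonferroni correction.

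**Conclusion.** The point holds as a selective and incorrectly named adjustment in the Statistical analysis section. Age and gender are covariates for the anatomical small-world and global parameters only. The functional contrasts and all nodal contrasts with HC are unadjusted as written, with no reason given.

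The size of any bias cannot be derived from the documents, which give no age gap, age-metric correlation or HC number. On the assumptions shown, the false rejection rate at an uncorrected 0.05 runs from 5.4% (0.25-year gap) to 11.4% (1-year gap). It stays at 5.0% if the analysed groups are balanced. These figures illustrate residual confounding and do not estimate it.

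The scope is the non-randomised HC contrasts. Active versus sham, the clinical outcomes and the sample size are untouched. It is worth correcting because the remedy is nearly free and uses covariates that the sponsor already plans to use.

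**What to change.** In Statistical analysis, replace both HC sentences with one rule: every comparison of network parameters between HC and patients with HFA, functional and structural, and for small-world, global and nodal measures alike, uses a linear model (ANCOVA) with group, age and sex as terms. Drop the t-test label for these contrasts.

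The cost is a change of wording, the same model run on more parameters, and two degrees of freedom per comparison (72 become 70 in the illustration). Age and gender are recorded for patients at baseline and are already planned as covariates for part of the HC comparison, so no new data are needed. If matching works, the adjustment does no harm.

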#### Structural network

The construction of structural networks based on diffusion imaging will also use AAL templates. Each brain region is referred to as a node, while detectable connections between nodes are considered edges. Two nodes are regarded as linked if at least one fiber bundle links them. For each subject, we calculate the weights of the edges using the connection density per unit of surface as its weights to obtain an undirected weighted structural connectivity network. Following that, the topological characteristics of the brain network will be assessed using graph theory. The thresholds for network groups will be quantified using a wide range of sparsity (0.05–0.5) with a 0.05 interval. To facilitate the study of the coupling between functional and structural connectivity networks, ensure structural connectivity networks are connected and have a minimum number of pseudo-edges (48).

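### The trial is sized on one CABS test at the full 0.05, but no primary test is named and the Bonferroni family is undefined, so the alpha for CABS is not settled.

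*Protocol article*

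**What the plan says.** Protocol article, Sample size estimation: "An alpha of 0.05 and a power of 0.9 are used in the study". The endpoint behind the calculation is CABS ("the Clancy Autism Behavioral Scale (CABS) score indicates a curative effect"), and "the mean and standard deviation of the paired differences are 5 and 8, respectively". The result is "a minimum requirement of 34 participants per group, accounting for an estimated 20% dropout rate", and after the allowance for unusable MRI data, "40 patients will be enrolled in each group, totaling 80 patients for the study".

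Protocol article, end of the Introduction: there are two primary objectives, the therapeutic effect and brain network remodelling. Neither is tied to a primary endpoint, visit or test. Table 1 lists five instruments (the high-functioning autism checklist, ABC, CABS, SRS and WISC) at baseline and at four later visits.

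Protocol article, Statistical analysis: effectiveness is judged by paired t-tests on mean scores before and after the intervention, with no scale singled out. The significance level is 0.05 for every test. The section then closes: "A Bonferroni correction will be performed on the t-tests utilized to examine group differences in behavioral and brain measurements". It gives neither the number of tests nor an exemption for CABS.

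**The concern.** The sample size rests on CABS being tested once at 0.05. The analysis section does not guarantee this, and its multiplicity sentence can be read in two ways.

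- **The correction includes the efficacy tests.** CABS is then tested at 0.05 divided by an unstated number, and the power of 0.9 was computed at an alpha that will not be used.
- **The correction covers only tests between groups.** The pre/post tests, which are the ones meant to establish effectiveness, then run at 0.05 each on several scales. With none set apart, success on any one could be presented as the trial's result.

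At stake is either the stated power or control of the false positive rate for the efficacy claim. Because the article does not say which applies, the choice could be made after the data are seen.

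**Working it through.** **Inputs.** From Sample size estimation: mean paired difference 5, SD 8 (standardised 0.625), alpha 0.05, power 0.90, dropout 20%, invalid MRI 15%, 40 enrolled per group. From Table 1: five instruments, or four if WISC is taken as an intelligence measure and not an efficacy scale. From Network analysis: five small-world properties and two global efficiencies, so seven measures. The family size m is not stated, so a range is shown.

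**Step 1: reproduce the plan's figure.** Paired normal formula, two-sided:

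n = (SD × (z₀.₉₇₅ + z₀.₉₀) / difference)² = (8 × (1.960 + 1.282) / 5)² = 26.9, so 27.

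27 / 0.80 = 33.75, so 34. Then 34 / 0.85 = 40. Both stated figures are reproduced. Other versions do not give them: one-sided 22, then 28; exact paired t 29, then 37; two-sample 54, then 68. The plan therefore spends the whole 0.05 on one test.

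**Step 2: power if CABS is inside a Bonferroni family.** Alpha = 0.05/m; exact paired power from the noncentral t with n − 1 degrees of freedom and noncentrality 0.625 × √n. Completers: 40 × 0.80 = 32.

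| m | alpha | power, n = 32 | power, n = 40 |
|---|---|---|---|
| 1 | 0.05 | 0.93 | 0.97 |
| 4 (scales without WISC) | 0.0125 | 0.81 | 0.90 |
| 5 (all instruments) | 0.01 | 0.78 | 0.89 |
| 12 (5 instruments + 7 brain measures) | 0.0042 | 0.67 | 0.81 |

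Under the plan's own normal formula, keeping 90% would need the following numbers per group (evaluable / after dropout / after the MRI allowance): 37/47/56 for m = 4, 39/49/58 for m = 5 and 45/57/68 for m = 12, against 27/34/40 in the plan.

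**Step 3: error rate if the efficacy tests are outside the family.** The chance of at least one false positive among k independent null tests at 0.05 is 1 − 0.95ᵏ: 0.19 for k = 4 and 0.23 for k = 5. Scales measured on the same child are likely to be correlated, which lowers these figures.

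**Step 4: power for an active-versus-sham primary test.** Take a between-arm difference of 5 and an SD of change of 8 in each arm, two-sided 0.05. The noncentrality is 5 / (8 × √(2/n)). At n = 32 per arm it is 2.5 and power is 0.69; at n = 40 it is 2.80 and power is 0.79. For 90%, n = 2 × 26.9 = 53.8, so 54 evaluable per arm, or 68 with 20% dropout. This shortfall arises from sizing on a paired test, before any multiplicity correction.

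**The case against.** The strongest reply is that the correction is worded for group differences, while the efficacy test is a within-group change and all tests are set at 0.05. Read literally, the paired CABS test keeps its 0.05 and the sizing stands. That reading is available. A reader might infer that the alpha actually used for CABS is certainly smaller than 0.05; the text does not support this as a fact. But the literal reading does not rescue the plan. The only between-arm behavioural test that the analysis section names is then the baseline comparison. Comparisons with healthy controls are possible, since they take the same tools, but they are not spelled out. The correction would protect nothing in the efficacy claim.

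A second reply is that the loss can be overstated, and this also stands in part. A reader might count five instruments at four post-baseline visits as 20 tests. However, comparing scores before and after the intervention fits baseline versus W12 better than every visit. A reader might likewise multiply the network measures by ten sparsity levels ("a wide range of sparsity (0.05–0.5) with a 0.05 interval"), two modalities and every brain region, and conclude that the imaging objective cannot be tested. The sparsity range is stated only for the structural network, and nothing says that each level is tested separately. Families of that size are hypothetical and are not relied on here. For four or five tests with all 40 analysed, power is close to 0.9, because the MRI allowance leaves slack for the clinical scales.

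Third, testing hierarchies are often left to an analysis plan. Missing detail would be no finding. Here the article itself states both a sizing alpha and a correction, and does not say how the two fit together.

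**Conclusion.** The point holds as an unresolved conflict between the sizing and the multiplicity rule. One of two things follows:

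- CABS is corrected, and the stated 0.9 is not met at 32 completers: 0.81 for four tests, 0.78 for five, and about 0.67 if seven brain measures join the family.
- The efficacy tests on four or five scales are uncorrected, with roughly a 19 to 23% familywise error rate under independence.

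The first figures assume the plan's difference of 5 and SD of 8 and its 20% dropout. The family of 12 assumes one value per brain measure in one modality. The second figures are upper values if the scales are positively correlated. The documents do not establish which branch applies.

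**What to change.** In Statistical analysis, state that the single primary test is active versus sham on CABS total at W12, two-sided 0.05, outside the Bonferroni family. Define the correction family for the other scales, and a separate one for the brain measures, for example with one summary value per measure across the sparsity range. The particular correction method is the sponsor's choice; what matters is that each family is listed.

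In Sample size estimation, restate the power for that contrast. With difference 5 and SD 8 it is about 69% at 32 per arm and 79% at 40 per arm. The sponsor should either accept that figure openly or revisit the sample size (54 evaluable per arm for 90%).

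The text change is small. The real cost is that only one endpoint carries the confirmatory claim, and the stated power becomes less favourable.
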